## Abstract

While the incidence of Human Immunodeficiency Virus (HIV) infection is decreasing in most age groups worldwide, it is rising among adolescents and young adults, who also face a higher rate of HIV-related deaths. This tech-savvy demographic may benefit from an online patient portal designed to enhance patient activation—empowering them to manage their health independently. However, the effectiveness of such digital health interventions on young HIV patients in Kenya remains uncertain. We will conduct a 12-month stepped wedge cluster randomized trial involving 15-24-year-old HIV patients with smartphone access. The primary outcome will be patient activation, with secondary outcomes including self-reported adherence, social engagement and viral suppression. We will also evaluate the portal’s functionality, usability, fidelity, and costs. Participants will be recruited from 47 antiretroviral treatment (ART) sites with electronic medical records (EMR), forming 16 clusters of 30 participants each. Clusters will be randomized into three sequences for intervention every three months. Baseline measurements (patient activation, adherence, social engagement and viral suppression) will be collected over two weeks, followed by checks at 3, 6, and 12 months. Data will be analyzed using generalized linear mixed models and adjusted for cluster effects and potential confounders. Results will be disseminated through stakeholder forums, scientific conferences, peer-reviewed publications, and the media.

## Introduction

Of the 37.7 million people living with the Human Immunodeficiency Virus (PLHIV) globally in 2020, 25.3 million resided in sub-Saharan Africa (SSA), where 460,000 of the 680,000 global acquired immune deficiency syndrome (AIDS) related deaths (ARD) also occurred [1]. While new infections are decreasing in other age groups, they continue to rise among adolescents and young people (AYP). In 2020 alone, 400,000 new cases were reported, with 150,000 occurring in individuals aged 10 to 19—an age group also reported to be disproportionately affected by ARD [2,3]. In Kenya, there were an estimated 1.4 million PLHIV, including 160,000 young people aged 15–24 by the end of 2020. Of the 33,000 new infections recorded in the same year, approximately 35% were among this younger age group [4]. As of January 2021, Kenya had nearly 60 million mobile phone connections, resulting in a mobile penetration rate of 108.9%. The country’s internet penetration stands at 40%, representing over 21 million people, about half of whom also used social media [5]. According to the International Telecommunication Union, young people in low- and middle-income countries (LMICs) are nearly three times more likely to be using the internet compared to the general population [6]. Despite this technological readiness, a recent review highlighted the lack of published interventions targeting the over 4 million young people aged 15–24 living with HIV globally, despite being identified as a “critical group experiencing multiple barriers to engagement in care.” [7]. Patient health portals offer a promising solution for this vulnerable population, who may be more likely to adopt digital health solutions compared to other age groups. To address this need, we developed the myCareHub digital health platform with input from the intended users, incorporating functionalities and mechanisms critical to patient activation (Fig 1) [8]. Grounded in the COM-B framework for behavior change, which posits that behavior is influenced by three key factors—capability, opportunity, and motivation—the platform is designed to address each of these elements to promote effective self-management of health (Fig 2) [9].

**Fig 1 pdig.0000380.g001:**
[figure not shown]
Mechanisms of patient activation—adapted from Otte-Trojel, de Bont [8].

**Fig 2 pdig.0000380.g002:**
[figure not shown]
COM-B theoretical framework for behaviour change.

The platform will be accessible via password-protected mobile phones to ensure data security and confidentiality, offering a range of services to both healthcare providers (HCPs) and patients (Fig 3).

**Fig 3 pdig.0000380.g003:**
[figure not shown]
Diagrammatic representation of myCareHub and functions available to use.

This study will evaluate whether myCareHub can improve patient activation among AYPs, leading to greater engagement in HIV care and treatment. In alignment with the World Health Organization (WHO) guidelines for mobile health evidence reporting and assessment (mERA), the study will also assess the quality, fidelity, and coverage of the platform, focusing on key program indicators often overlooked in published studies (Fig 4) [10].

**Fig 4 pdig.0000380.g004:**
[figure not shown]
Life cycle of a digital intervention.

The results of this study will inform HIV programming for young people and other vulnerable populations, contribute to digital health policy, and play a key role in advancing the global goal of eliminating AIDS as a public health threat by 2030.

## Materials and methods

### Setting

The study will take place as part of a large antiretroviral therapy (ART) program in partnership with the Kiambu and Kirinyaga county health departments. The program currently supports HIV-related prevention, care, and treatment activities at 78 public healthcare facilities, with 47 of these facilities equipped with electronic medical records (EMR) systems.

For this study, the 47 EMR-enabled facilities will be clustered based on geographical proximity, roughly coinciding with sub-county territorial boundaries. At study inception, the program provided ART to 38,079 PLHIV, including 3,459 (9%) AYP aged 15–24. Around 89% of the target population is enrolled at the 47 EMR sites, which will be the primary focus for participant recruitment.

### Study design

This is a multicenter stepped wedge cluster randomized trial designed to evaluate the impact of the myCareHub patient portal on improving patient activation and clinical outcomes among HIV- positive AYP aged 15–24 years. Participants will be recruited from 47 EMR-enabled ART clinics (Table 1).

**Table 1 pdig.0000380.t001:** PICOT framework.

Population	Adolescents and young persons aged 15–24 years, who are living with HIV and are receiving care at an EMR-enabled Anti-Retroviral Treatment (ART) site. All participants will have ready access to a smartphone, which is necessary for using the myCareHub portal.
Intervention	Implementation and testing of the myCareHub patient health portal. This portal is designed with several functionalities that support behavior change according to the COM-B framework. These include e-learning resources, an online patient diary, peer-to-peer networking, patient-reported outcomes, and personalized care triggered by interaction with healthcare providers (HCPs).
Comparator	Standard of care patient engagement strategies, which involve traditional in-person clinic visits, standard ART support, and typical adherence and social engagement practices without the use of the myCareHub digital health portal.
Outcome	The primary outcome of the study is patient activation, which will be measured using the Patient activation measure (PAM). Secondary outcomes include viral load suppression, social engagement (assessed using the Social support questionnaire [SSQ6]), self-reported ART adherence, and portal usage metrics (e.g., login frequency, time spent, interaction with portal features).
Time	The study will span a total of 15 months. Initially, there will be a control period of 3 months, during which clusters will receive standard care. Intervention sequences will be rolled out every 3 months, with measurements taken at baseline and every three months for each cluster. After all clusters have received the intervention, a 6-month observation period will follow.

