**Abbreviations**: TO–baseline, T1 –time period 1, T2 –time period 2, T3 –time period 3, T4 –time period 4. Mo–month. PAM–patient activation measure. VLS–viral load suppression. SSQ6- social support questionnaire short form. MAUQ–mHealth App usability questionnaire. TB ICF–tuberculosis intensified case finding. PHQ-9 –patient health questionnaire– 9 items, SGBV–sexual and gender-based violence, CRAFFT–car, relax, alone, forget, friends, trouble. **NB**: The third sequence is extended to ensure that the final stratum completes a minimum of six months, which is the recommended duration for adequately assessing patient activation.

To minimize heterogeneity between clusters, stratification was applied based on size (small, medium, large), sex (male, female), and viral load suppression (VLS). This stratification created comparable blocks of clusters prior to randomization, ensuring balance across the intervention groups (Table 3). Clusters were then randomly assigned to one of three sequences for the time of crossover from control to intervention using a computer-generated random number list (Table 4). Each cluster will begin in the control period and transition to the intervention at staggered intervals, with clusters randomized to groups of five or six. Each intervention sequence will last three months, with a two-week interval between sequences to allow for baseline measurements and smooth implementation of the intervention. The third sequence will extend for six months to allow for additional measurements (Table 2).

**Table 3 pdig.0000380.t003:** Sub-counties by key attributes.

Sub-county	Number of AYP ^b^	Size strata	VLS ^a^ 15–19	VLS 20–24	Cohort retention	Males (%)
Thika town	632	Large	80%	90%	89%	41%
Ruiru	330		84%	89%	68%	25%
Kiambu town	205	Medium	86%	89%	100%	32%
Kiambu Central	176		86%	90%	84%	55%
Gatundu South	166		61%	90%	50%	40%
Juja	146		91%	82%	67%	35%
Kiambaa	123		87%	91%	100%	27%
Kirinyaga South	116		91%	87%	88%	53%
Githunguri	113		85%	89%	100%	27%
Kabete	110		94%	94%	100%	23%
Gatundu North	107		92%	89%	100%	40%
Limuru	103		90%	100%	100%	35%
Kirinyaga West	88	Small	81%	92%	74%	37%
Kikuyu	73		100%	90%	100%	16%
Kirinyaga East	58		100%	86%	87%	57%
Lari	51		100%	91%	100%	23%
Kirinyaga North	50		60%	68%	88%	48%

^a^ viral load suppression

^b^ adolescents and young persons

**Table 4 pdig.0000380.t004:** Randomization of clusters into sequences.

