#### Antiretroviral therapy adherence questionnaire

To assess medication adherence in participants, we will use a customized ART Adherence Questionnaire utilizing a visual analogue scale (VAS) to estimate self-reported adherence over the past 30 days. Similar VAS measures have been well-validated in previous studies, demonstrating their reliability and simplicity for capturing self-reported adherence, particularly in diverse patient populations [12–14]. In addition to the VAS, our tool incorporates questions about the timing of missed doses and the reasons for non-adherence such as being away from home, forgetting, or concerns about side effects. This adherence measure enables both a visual and quantitative reflection of participants’ adherence behaviors, facilitating tracking of adherence patterns across the study. This tool will be administered at 3, 6 and 9 months.

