#### Statistical analysis of secondary objectives

*Self-reported medication adherence*. Self-reported adherence scores, collected at baseline, 3, 6, and 9 months, will be analyzed using GLMMs. These models will account for correlations between repeated measures across the different time points and clustering effects within facilities. The percentage of adherence in the intervention versus control groups will be compared, with adjustments made for potential confounders such as age, sex, and ART duration.

*Viral load suppression*. The proportion of patients achieving viral load suppression (VLS) at baseline, 3, 6, and 9 months will be modeled using logistic regression, adjusted for cluster effects. A comparison between the intervention and control groups will be made, considering time effects and covariates. The percentage of participants in each group who achieve viral suppression will be reported, and changes over time will be assessed.

*Social engagement*. Social engagement scores (SES) from the SSQ6 will be compared across time points (baseline, 3, 6, 9 months) using mixed-effects models. Participation in online communities will be tracked and compared to baseline scores to assess whether the intervention effectively improves social engagement. Differences in social engagement over time will be explored, with subgroup analyses based on age, sex, and baseline social support.

*Portal use and engagement metrics*. The frequency of portal logins, time spent on the portal, and functionalities accessed will be analyzed using descriptive statistics. Regression models will be used to explore relationships between portal use and adherence, activation, and viral suppression outcomes. Portal use will be summarized as engagement metrics (e.g., total logins, average time spent) and correlated with clinical outcomes, including adherence and viral suppression.

*Usability and acceptability scores*. Usability scores from the MAUQ and the custom-designed acceptability survey will be analyzed using descriptive statistics and compared across subgroups (age, sex, ART duration). Generalized linear models will be used to explore the association between usability scores and primary or secondary outcomes. Usability and acceptability will be assessed and reported, with particular attention to how these factors influence engagement with the platform.

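### Trial length, month zero and survey times are not reconciled, and neither reading of the 6- and 9-month primary outcome works for the last sequence

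*Protocol article*

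**What the plan says.** **Duration.** The abstract states: "We will conduct a 12-month stepped wedge cluster randomized trial". Table 1 (Study design) states: "The study will span a total of 15 months. Initially, there will be a control period of 3 months, during which clusters will receive standard" … It adds roll-out in three-month steps, surveys at baseline and then quarterly, and six months of observation once every cluster has crossed over.

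**Calendar.** Table 2 (Justification for the stepped wedge design) opens with a T0 control column of no stated length and a two-week baseline survey. Four periods follow (months 1–3, 4–6, 7–9 and 10–12), each closed by a two-week survey, T1 to T4. Sequence 1 is on intervention from month 1, sequence 2 from month 4 and sequence 3 from month 7. The note explains the last period: "The third sequence is extended to ensure that the final stratum completes a minimum of six months", which it calls the recommended duration for assessing activation adequately.

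**Survey times.**
- Abstract: baseline, "followed by checks at 3, 6, and 12 months".
- Table 2: T0 to T4, with PAM, adherence and viral suppression at each.
- Table 5: baseline, 3, 6 and 9 months for PAM, adherence, viral suppression and the cluster outcomes. The sentence introducing it also mentions an end-line measurement.
- Statistical analysis of secondary objectives: "Self-reported adherence scores, collected at baseline, 3, 6, and 9 months, will be analyzed using GLMMs". Viral suppression has the same list.
- Antiretroviral therapy adherence questionnaire: "This tool will be administered at 3, 6 and 9 months", with no baseline.
- Variable selection: the primary outcome is PAM change at 6 and 9 months.

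**The concern.** In a stepped wedge trial the calendar decides which observations count as control, which count as intervention, and how long each sequence has been exposed at each survey. Here the abstract has no month 9, Table 5 and the analysis text have no month 12, and Table 2 has both. The time points of the primary outcome stop at 9. The survey that could be left out is T4, the one that the extension of the third sequence exists to supply. Two analysts working from this text could put different PAM data into the primary comparison, and each could cite the protocol in support.

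**Working it through.** **Inputs.** Table 1: 3-month control period, 3-month steps, three sequences, 6 months after the last crossover. Table 2: crossovers at the start of months 1, 4 and 7 (0, 3 and 6 months elapsed), four 3-month periods, five 2-week surveys. Table 4: 6, 6 and 4 clusters; 186, 170 and 124 participants. Table 2 labels its last group as six clusters; the exposure arithmetic does not depend on which is used.

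**Step 1: reproduce the stated duration.** Control period + (sequences − 1) × step + follow-up = 3 + 2 × 3 + 6 = 15 months. Table 1 is internally consistent.

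**Step 2: Table 2's duration.** Its numbered months give 4 × 3 = 12. Five two-week gaps (10 weeks, about 2.3 months) make it about 14.3. If T0 is the three-month control period of Table 1, the total is 3 + 12 = 15 before gaps.

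**Step 3: exposure at each survey** = survey month − crossover month.

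| Study month | Seq 1/2/3, Table 2 clock (crossovers 0, 3, 6) | Seq 1/2/3, Table 1 clock (crossovers 3, 6, 9) |
|---|---|---|
| 3 | 3 / 0 / control | 0 / control / control |
| 6 | 6 / 3 / 0 | 3 / 0 / control |
| 9 | 9 / 6 / 3 | 6 / 3 / 0 |
| 12 | 12 / 9 / 6 | 9 / 6 / 3 |
| 15 | – | 12 / 9 / 6 |

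(0 means surveyed at the point of crossover, so still a control observation.)

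**Step 4: apply the primary time points, 6 and 9 months.**
- *As study months, Table 2 clock:* the last named survey finds sequence 3 at 9 − 6 = 3 months of exposure. Its six-month value, at T4, is not among the named times.
- *As study months, Table 1 clock:* sequence 3 is at 9 − 9 = 0 months.
- *As months since crossover:* sequence 3 reaches 12 − 6 = 6 months at T4. Nine months would need a survey three months after T4, and none is planned.

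Sequence 3 is 4 of 16 clusters and 124 of 480 participants (26%).

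**Step 5: which reading does the text favour?** Table 2's survey labels (T1: 3; T2: 3, 6; T3: 3, 6, 9; T4: 6, 9, 12) match exactly the months since crossover of the sequences then on treatment. Table 5 points the other way. It uses the same times for control and intervention observations and for cluster programme data, although a control observation has no time since crossover. It also gives usability and acceptability a separate end-point measurement and does not assign PAM to it. The text does not settle the matter.

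**Step 6: power with and without T4.** The stated 27 per cluster at 90% power cannot be reproduced, because the SD is taken from a cited study and not printed, and Fig 5 is not shown. Only a relative check is possible. Assume the stated ICC of 0.02 and individual autocorrelation (IAC) of 0.8, m = 27, a 5-point effect, cluster autocorrelation (CAC) of 0.3 to 1.0, and alpha 0.05 (printed as 0.05%). The covariance of a cluster's survey means is

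V = SD² × {[ICC·CAC + (1 − ICC)·IAC/m]·J + [ICC·(1 − CAC) + (1 − ICC)(1 − IAC)/m]·I},

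where J is the all-ones matrix and I the identity. The generalised least squares SE of a constant treatment effect, adjusted for survey, gives power = Φ(5/SE − 1.96). With SD solved so that T0–T4 gives 90% (about 24 to 41 points), dropping T4 gives 86.7% to 87.6% over allocations of 6/6/4 and 5/5/6. For assumed SDs of 12 to 20 with CAC 0.9, power is about 100% either way.

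**The case against.** The best defence is that the calendar is less broken than it looks, and much of that defence stands.

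- A reader might infer that the last sequence never gets six months of exposure. The documents do not support this: Table 2 keeps sequence 3 on intervention through months 7–12 and surveys PAM, adherence and viral suppression at T4. Only the analysis of that survey is in doubt.
- A reader might infer that Tables 1 and 2 cannot both be followed by a site in sequence 1, or that they imply different numbers of control surveys. Neither is established. If the T0 column is Table 1's control period, both tables give 15 months and both leave six months after the last crossover; the abstract's 12 months could then count from the first crossover. Against this, nothing says that T0 lasts three months: the Table 2 abbreviations call it only baseline.
- A reader might infer from the adherence questionnaire section that sequence 1 would have no control-period adherence value. Baseline adherence is stated in the abstract, Table 2, Table 5 and the secondary-analysis text, so the missing word is an omission to correct and no more.
- Table 2's labels suit months since crossover, and the text introducing Table 5 mentions end-line. On that reading T4 supplies the six-month value for sequence 3 and the nine-month value for sequence 2. It still gives no nine-month value for sequence 3.

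The defence narrows the point but does not remove it. Nor is this detail that can be left to an analysis plan, because the article itself fixes the conflicting times.

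**Conclusion.** The point holds as a failure to reconcile. Duration is 12 months in one place and 15 in another, the survey lists differ in three ways, and month zero, the length of T0 and the meaning of the month labels are undefined. It matters because it reaches the primary outcome. On Table 2's clock, study months leave the named PAM values for sequence 3 at no more than 3 months of exposure, against a stated minimum of six. Months since crossover leave sequence 3 unable to supply one of the two primary time points. Under a constant-effect model the loss of power from omitting T4 is small, from 90% to about 87%. The consequence is mainly the exposure time at which the effect is measured and how observations are classified. The exposure figures assume crossovers as drawn in Table 2; the power figures rest on a back-solved SD and alpha of 0.05.

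**What to change.** Reconcile the abstract, Table 1, Table 2, Table 5, Variable selection, the adherence questionnaire section and the secondary-analysis text to one calendar:

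1. Define month zero and state the length of the T0 control column.
2. Use one survey list in study time, T0 to T4, throughout.
3. State that all five surveys, including T4, enter the PAM, adherence and viral suppression models, and show the exposure of each sequence at each survey in Table 2.
4. Define the primary time point so that every sequence can contribute to it.
5. Add baseline to the adherence questionnaire section, to match Table 2, Table 5 and the secondary-analysis text.

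Usability and acceptability scores need no baseline, since they presuppose use of the portal. The cost is wording only: T0 and T4 are already planned, so no new data collection follows. The choice should be recorded before outcome data are analysed.

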### Justification for the stepped wedge design

The stepped wedge design was chosen to mitigate contamination bias. In a facility-based setting, randomizing individuals to control or intervention groups within the same facility would result in unintentional exposure of the control group to the intervention. The staggered implementation across clusters also enables continuous refinement of the myCareHub platform based on feedback from earlier clusters, thus improving the intervention over time.

A minimum sample of 480 AYP will be recruited into 16 clusters using a stepwise design, with three-month intervals between successive steps (Table 2).

**Table 2 pdig.0000380.t002:** Study design—cluster randomized trial utilizing a stepped wedge design with 16 clusters and 3 sequences.

CLUSTERS (11–16)	CONTROL	T0.: Baseline survey: Demographics, clinical enquiry, baseline PAM, adherence, VLS, social engagement scores on SSQ6, cluster level retention, cluster VLS.	CONTROL	T1 survey: 3 Mo PAM, adherence, VLS, portal measures: TB ICF, PHQ-9, CRAFFT, SGBV screening, Contraceptive use intention. Feedback on portal, cluster level retention, cluster VLS.	CONTROL	T2 survey: 3, 6 Mo PAM, adherence, VLS, retention, portal measures: TB ICF, PHQ-9, CRAFFT, SGBV screening, Contraceptive use intention. Feedback on portal, cluster level retention, cluster VLS.	INTERVENTION	T3 survey: 3, 6, 9 Mo PAM, adherence, VLS, retention, portal measures: TB ICF, PHQ-9, CRAFFT, SGBV screening, Contraceptive use intention, feedback on portal, cluster level retention, cluster VLS.	INTERVENTION	T4 survey: 6,9 & 12 Mo PAM, adherence, VLS, MAUQ, acceptability score, portal measures: TB ICF, PHQ-9, CRAFFT, SGBV screening, Contraceptive use intention, feedback on portal, cluster level retention, cluster VLS.
CLUSTERS (6–10)					INTERVENTION					
CLUSTERS (1–5)			INTERVENTION							
**TIME**	**TO**	**2 weeks**	**T1** **Mo 1–3**	**2 weeks**	**T2** **Mo 4–6**	**2 weeks**	**T3** **Mo 7–9**	**2 weeks**	**T4** **Mo 10–12**	**2 weeks**

**Abbreviations**: TO–baseline, T1 –time period 1, T2 –time period 2, T3 –time period 3, T4 –time period 4. Mo–month. PAM–patient activation measure. VLS–viral load suppression. SSQ6- social support questionnaire short form. MAUQ–mHealth App usability questionnaire. TB ICF–tuberculosis intensified case finding. PHQ-9 –patient health questionnaire– 9 items, SGBV–sexual and gender-based violence, CRAFFT–car, relax, alone, forget, friends, trouble. **NB**: The third sequence is extended to ensure that the final stratum completes a minimum of six months, which is the recommended duration for adequately assessing patient activation.

To minimize heterogeneity between clusters, stratification was applied based on size (small, medium, large), sex (male, female), and viral load suppression (VLS). This stratification created comparable blocks of clusters prior to randomization, ensuring balance across the intervention groups (Table 3). Clusters were then randomly assigned to one of three sequences for the time of crossover from control to intervention using a computer-generated random number list (Table 4). Each cluster will begin in the control period and transition to the intervention at staggered intervals, with clusters randomized to groups of five or six. Each intervention sequence will last three months, with a two-week interval between sequences to allow for baseline measurements and smooth implementation of the intervention. The third sequence will extend for six months to allow for additional measurements (Table 2).

**Table 3 pdig.0000380.t003:** Sub-counties by key attributes.

Sub-county	Number of AYP ^b^	Size strata	VLS ^a^ 15–19	VLS 20–24	Cohort retention	Males (%)
Thika town	632	Large	80%	90%	89%	41%
Ruiru	330		84%	89%	68%	25%
Kiambu town	205	Medium	86%	89%	100%	32%
Kiambu Central	176		86%	90%	84%	55%
Gatundu South	166		61%	90%	50%	40%
Juja	146		91%	82%	67%	35%
Kiambaa	123		87%	91%	100%	27%
Kirinyaga South	116		91%	87%	88%	53%
Githunguri	113		85%	89%	100%	27%
Kabete	110		94%	94%	100%	23%
Gatundu North	107		92%	89%	100%	40%
Limuru	103		90%	100%	100%	35%
Kirinyaga West	88	Small	81%	92%	74%	37%
Kikuyu	73		100%	90%	100%	16%
Kirinyaga East	58		100%	86%	87%	57%
Lari	51		100%	91%	100%	23%
Kirinyaga North	50		60%	68%	88%	48%

^a^ viral load suppression

^b^ adolescents and young persons

**Table 4 pdig.0000380.t004:** Randomization of clusters into sequences.

Cluster	15–19 years old	20–24 years old	Total AYP ^a^	Strata Size	Random number	Sequence	No. of AYP (n = 480)
Juja	48	98	146	Medium	0.91	1	186
Kiambaa	30	80	110	Medium	0.84	1	
Kirinyaga Central	76	83	159	Medium	0.64	1	
Kabete	19	75	94	Small	0.97	1	
Kirinyaga South	27	48	75	Small	0.83	1	
Ruiru	77	253	330	Large	0.73	1	
Gatundu South	75	91	166	Medium	0.56	2	170
Gatundu North	52	55	107	Medium	0.55	2	
Limuru	41	62	103	Medium	0.54	2	
Lari	12	23	35	Small	0.70	2	
Kirinyaga East	29	26	55	Small	0.57	2	
Thika Level 5	172	196	368	Large	0.23	2	
Githunguri	45	56	101	Medium	0.46	3	124
Thika Town	102	135	237	Medium	0.38	3	
Kiambu Township	87	112	199	Medium	0.06	3	
Kirinyaga West	29	42	71	Small	0.51	3	

^a^ adolescents and young people

